The retention of a complete dental prosthesis by a single implant placed in the midline has arisen as a minimal implant-based treatment modality for the edentulous mandible. Single implant overdentures present potential advantages that may lead to their choice for certain patients. These advantages include reduced costs involved with the provision of dental care. This treatment can be especially advantageous for patients with low functional demands, such as the elderly [11]. Other benefits for this specific population include minimum operative time and low morbidity. This latter aspect seems strongly correlated to the number of installed fixtures rather than their dimensions, at least when considering the anterior edentulous mandible [12].

Outcomes of single implant overdentures are favorable considering patient satisfaction [13, 14] and oral health-related quality of life [15, 16]. These measures are substantially increased after loading a single mandibular implant in conventional denture wearers. When compared to two-implant overdentures, differences in terms of patient satisfaction and oral health-related quality of life were reported to be insignificant [13, 16]. In addition, a recent systematic review revealed no significant between-treatment differences in terms of implant survival [17]. However, treatment success rates tend to improve when avoiding immediate loading [16] and machined implants [14].

From the biomechanical standpoint, the use of a single implant is not associated with poorer fixture behavior. Maeda et al. [18] observed a favorable incidence of forces on fixtures when comparing single implant-retained mandibular overdentures to a two-implant retained prosthesis. This was found for both dome-shaped magnets and O-ball attachments. A finite element method simulation of mandibular overdentures suggests that single implants undergo favorable strain compared to numbers in the range of 2–4, without harmful loading on abutments, peri-implant bone, or the edentulous ridge [19]. Furthermore, the placement of an implant in the midline does not appear to increase the incidence of denture fractures when compared to two-implant overdentures [20].

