### Study outcomes

All patient-reported outcomes, except for prosthesis rotation, will be collected at baseline, together with sociodemographic data, including age, gender, level of education, and income. Clinical data will be also collected before treatment, such as ridge morphology [28], amount of time edentulous, and age of existing dentures.

Participants will return for outcome assessment after three months using each attachment, for a total follow-up time of six months. A three-month period is enough to observe a significant decrease in the retention force of Locators [29] but is of unlikely length for adverse events associated with other components. Moreover, a slightly longer period, i.e. six months, results in similar patient satisfaction with mandibular overdentures [30]. Participants will be evaluated again 12 months following the cross-over trial for an appraisal of maintenance needs/adverse events. A 12-month period will be enough to reveal attachment maintenance events for most participants with Locators [21], as well as some uncommon events, e.g. denture base fractures [13].

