### Statistical analysis

All quantitative data will be entered and analyzed in a blinded fashion. Such data will undergo descriptive analysis and will be transformed in cases of considerable deviation from normality. Clinical data will generate a composite variable representing clinical adversities; both the compound measure and separate event types will be analyzed.

Mixed linear models will be used to test the effect of interventions and follow-up time (three vs six months), as well their interaction.

The primary outcome will be further tested for carryover effects by fitting another mixed linear model with the two treatment periods and testing for the intervention by period interaction. Other approaches to assess the primary outcome will involve the inclusion of the randomization strata (ridge shape), age, baseline results, and perceived denture base rotation as covariates in separate models, one covariate each time. Analysis for carryover will be performed for cost estimates.

Results will be evaluated according to the intention-to-treat principle. In the case of unbalanced missing data among interventions or loss of 5% (*n* > 1) or more of participants, different strategies will be attempted for imputing primary outcome data, as recommended by Dziura et al. [43]; multiple imputation will be used for patient satisfaction based on least squares regression with at least five datasets. In the case of “missing not at random” (MNAR) data, we will repeat analyses after a baseline-observation-carried-forward approach (i.e. withdrawn participants will be considered as dissatisfied as before receiving implants). A second analysis will be performed with imputed values and cross-checked. Statistical tests will be performed using SPSS 21.0, considering α = 0.05.

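### The fallback for data judged missing not at random carries the pre-implant score into a cross-over in which both periods are on the implant, so it can create or mask an attachment difference

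*Protocol article*

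**What the plan says.** The Statistical analysis section handles missing primary-outcome data in steps.

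- The main analysis is a mixed linear model with intervention, follow-up time and their interaction.
- The trigger for imputation reads "In the case of unbalanced missing data among interventions or loss of 5" per cent or more of participants, glossed as more than one person. The plan then says that "different strategies will be attempted for imputing primary outcome data", and the same sentence goes on to name the method: "multiple imputation will be used for patient satisfaction based on least squares regression with at least five datasets".
- If data are missing not at random, "we will repeat analyses after a baseline-observation-carried-forward approach", explained as "withdrawn participants will be considered as dissatisfied as before receiving implants".
- Analyses on imputed values are to be cross-checked. No rule says what follows if the results disagree.

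Three other places matter. Under Study outcomes, "All patient-reported outcomes, except for prosthesis rotation, will be collected at baseline"; no baseline for the second period is described. Under Design and Attachment systems, the two three-month periods follow each other without washout, and both are on the same implant. The Background says of satisfaction and quality of life after single-implant treatment: "These measures are substantially increased after loading a single mandibular implant in conventional denture wearers".

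**The concern.** The primary hypothesis compares two attachments on the same implant. The baseline score belongs to a third condition, the conventional denture with no implant.

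In a parallel-group trial, carrying baseline forward penalises the arm that lost the participant. In this cross-over, a missing second period pairs an on-implant score for the first attachment with a pre-implant score for the second. The within-person difference is then implant versus no implant. The attachment penalised is the one that the sequence placed second.

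The rule also fits the likely state of withdrawn participants poorly. The section on risks and participant safety describes return to a conventional denture only after a failed implant that is not replaced. Most others who withdraw would still have the implant.

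Finally, the rule is conditional on data being missing not at random, which the observed data cannot establish. At stake is whether the sensitivity analysis tells readers anything reliable about how robust the attachment comparison is.

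**Working it through.** **Inputs from the protocol.** Minimally important difference 10 mm; SD of the difference 7.5 mm; 21 evaluable participants; two sequences at 1:1. The planned total reproduces as 21 × 1.2 = 25.2, rounded up to 26, which allows for 26 − 21 = 5 dropouts. Two-sided alpha is 0.01 under Sample size estimation and 0.05 under Statistical analysis, so both are shown.

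**Assumptions.** 13 per sequence; all five losses in period 2; implant gain over baseline G = 30 mm (range 20 to 40), averaged over the two attachments; SD of the gain 15 mm (not varied). The protocol gives neither the gain nor its SD.

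**Estimator.** Write A for Novaloc and B for Locator. The effect A − B is ½ × [mean(y1 − y2) in sequence A-B + mean(y2 − y1) in sequence B-A].

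**Bias with no true difference.** A period-2 dropout has y1 − y2 = G. With a dropouts in A-B and b in B-A:

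bias = ½ × (aG/13 − bG/13) = G(a − b)/26.

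Per unmatched dropout this is 20/26 = 0.8, 30/26 = 1.15 and 40/26 = 1.5 mm.

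| Split a/b | Bias at G = 20 / 30 / 40 (mm) | Type I error at 0.05, G = 20 / 30 / 40 | Type I error at 0.01, G = 30 |
|---|---|---|---|
| 3/2 | 0.8 / 1.2 / 1.5 | 0.017 / 0.007 / 0.001 | 0.000 |
| 4/1 | 2.3 / 3.5 / 4.6 | 0.080 / 0.082 / 0.073 | 0.008 |
| 5/0 | 3.8 / 5.8 / 7.7 | 0.304 / 0.516 / 0.686 | 0.127 |

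Error rates come from 20,000 simulated trials per cell, using a pooled t-test on 24 degrees of freedom and dropout unrelated to scores.

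**How likely each split is.** If dropout is unrelated to sequence, a 5/0 split in either direction has probability 2 × 1287/65780 = 4%. For 4/1 it is 2 × 715 × 13/65780 = 28%, and for 3/2 it is 2 × 286 × 78/65780 = 68%.

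**Near-balanced loss.** The shifts largely cancel in the treatment effect and move into a spurious period effect of G(a + b)/26, which is 30 × 5/26 = 5.8 mm for 3/2. The spread rises. With a proportion p of a sequence imputed, the SD is √(7.5² + p(1 − p)G²), which gives 14.7 mm for p = 3/13 and 13.2 mm for p = 2/13, instead of 7.5. This formula keeps 7.5 mm for the dropouts too, so it is a low figure if gains vary more. For a true 10 mm difference and a 3/2 split, simulated power at alpha 0.01 is 92%, 80% and 58% for G = 20, 30 and 40. At alpha 0.05 it is 99%, 97% and 93%. Analysing only the 21 completers would give 99.8% at alpha 0.01.

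**Masking.** Take a true difference of 10 mm in favour of A, G = 30, and most losses in sequence B-A. A dropout there contributes −G + 5 = −25, and one in A-B contributes 30 + 5 = 35.

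- 0/5: ½ × [10 + (8 × 10 − 5 × 25)/13] = 3.3 mm.
- 1/4: ½ × [(12 × 10 + 35)/13 + (9 × 10 − 4 × 25)/13] = 5.6 mm.

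With the splits reversed, the same sums give 14.8 mm (5/0) and 12.5 mm (4/1).

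**Both periods missing.** The imputed difference is 0. Five such participants shrink a 10 mm effect to 10 × 21/26 = 8.1 mm.

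**Caveat on the SD.** The stated 21 is reproduced only if 7.5 mm is a within-period SD, so that the SD of the difference is 7.5 × √2 = 10.6 mm. With 7.5 mm as labelled, 12 or 13 participants suffice. The biases above do not depend on this; the error rates and power do.

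**The case against.** The strongest defence is that little depends on this rule. It is a conditional repeat, after multiple imputation. A reader might infer that dropouts are generally scored at baseline, or that the primary result depends on it. The text does not support either reading. Nor does it support the inference that no analysis is designated: the sentence that speaks of attempting several strategies goes on to name multiple imputation. What is missing is only a rule for conflicting results.

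The large error rate also needs care. The figure of about 52% requires all five losses in one sequence, all in period 2, and unrelated to scores. The plan would invoke the rule when losses are thought to be related to scores. If people leave because they dislike the second attachment, a penalty on that attachment is in the right direction, though crude. After a failed, unreplaced implant, a baseline-like score is plausible.

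These points stand, and they limit the weight of the concern without removing it. The penalty equals the benefit of having an implant, which says nothing about how much worse one attachment is than the other. It applies whatever the reason for withdrawal. One of the plan's two triggers, missing data unbalanced between interventions, is the situation in which the shifts fail to cancel.

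Predictors and delta values could be left to an analysis plan that is not shown. The choice of baseline carried forward, however, is fixed in the article.

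**Conclusion.** The point holds as a badly chosen sensitivity analysis, and correcting it is worthwhile. Followed as written, it mixes an implant-versus-no-implant contrast into an attachment comparison.

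At an assumed gain of 30 mm with five period-2 losses, the likeliest split (3/2) gives a minor bias of 1.2 mm, but the variance inflation makes the test conservative and costs power. A 4/1 split shifts the estimate by about a third of the minimally important difference, yet raises the type I error at 0.05 only to about 8%. The 5/0 result is an extreme case and should not be read as the trial's error rate. A reader might also infer that the whole implant benefit passes to the first attachment in the trial estimate. That is true only for an individual with period 1 alone; in the trial estimate only the imbalance between sequences counts.

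The mechanism follows from the protocol's own text. The sizes rest on the assumed gain and its SD, equal sequences, and losses confined to period 2.

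**What to change.** - Keep the mixed model on all available period scores and the planned multiple imputation as the reference analyses.
- Replace baseline carried forward with delta-adjusted multiple imputation. Condition on the participant's observed on-implant score, sequence, period and baseline. Subtract a penalty from imputed scores for one attachment at a time, for example 5, 10 and 15 mm, up to the tipping point. A 10 mm penalty then moves the estimate by 10/26 = 0.4 mm per unmatched dropout, whatever the implant gain.
- Run it whenever the missing-data trigger is met, not only when data are declared missing not at random.
- State that the reference analysis carries the conclusion and that the tipping point is reported beside it.

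The cost is some extra programming, which can be done in SPSS. No new data are needed.

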### Qualitative assessment

A qualitative assessment will follow the quantitative phase to better understand any emergent themes in addition to the following: (1) patients’ reasons for choosing one attachment system; (2) their perceptions of the advantages and disadvantages of each attachment; and (3) their experience of living with a single implant to retain their mandibular overdentures. We will adopt a descriptive approach [44], conducting individual semi-structured interviews, that constitutes a powerful method to obtain an in-depth understanding of patients’ experiences and preferences [45].

We will conduct individual semi-structured interviews with all study participants (n = 26). The interviews will be held outside of the clinics in a place conducive for a confidential discussion. An experienced research associate will use an interview guide that describes the interview procedure and contains open-ended questions on the abovementioned themes. Since this is an explanatory mixed-methods design, we will follow appropriate guidelines, in that the interview guide will be developed based on the results of the quantitative outcomes and on which results require further explanation or clarification. Participants will be encouraged to express themselves spontaneously in a conversational manner. Each interview (about 1 h long) will be digitally recorded and transcribed; the transcription will serve as the basis for qualitative data analysis.

The analyses will consist of several stages: (1) summarizing each interview using a contact summary sheet; (2) coding the transcribed interviews; and (3) summarizing and interpreting the data. The contact summary sheet, as recommended by Miles et al. [46], will be completed immediately following each interview and provide a preliminary assessment of important findings. Coding of the transcribed interviews under each theme will be done with N’Vivo software (QSR). To improve coding quality, the research associate and one of the researchers will undertake to compare two transcripts chosen at random: each will code these accounts independently and then meet to compare results and to revise the codes when necessary. The research associate and the researchers will then identify and describe all relevant themes related to our research objectives.

### Integration of datasets

Quantitative and qualitative datasets will be compared to assess their eventual correspondence. This will be done by a follow-up of results with a joint display [47] of both sets to determine whether quantitative patient satisfaction and preferences can be explained by qualitative findings.

### Long-term follow-up

Once participants provide six-month data and choose the attachments they wish to keep, they will receive new polymeric components. Some participants might prefer to have no specific preference; in that case, we will keep the last type used. Then, we will schedule them for another appointment after 12 months, during which session the same outcome data will be gathered. The same statistical strategies will be employed for the analysis of these long-term data.

In the meantime, participants may contact the research team for unscheduled appointments. Any event, such as maintenance and clinical complications, as well as time and procedures carried out, will be reported as part of the collected outcome data.

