In this mixed-methods randomized cross-over trial (RCT), we aim to produce evidence of the efficacy of using the Novaloc attachment system to retain single-implant mandibular overdentures, compared to a traditional cylindrical attachment (Locator), for edentate elder patients. The primary outcome of this study is ratings of general satisfaction on visual analog scale (VAS) measures following three months of use with each attachment type. Through qualitative interviews, we will also describe what characteristics of these systems are considered important to patients when stating their satisfaction and preferences; we will use this rich descriptive data to help explain the quantitative RCT results.

Secondary outcomes include: (1) specific domains of satisfaction (e.g. retention/stability and hygiene); (2) oral health-related quality of life (OHIP-EDENT); (3) economic variables; (4) perceived rotation of the mandibular overdenture; (5) clinician-based outcomes, i.e. success rate of implants/overdentures and clinical complications/maintenance needs; and (6) choice of attachment.

Participants will keep their chosen attachments for another 12-month period and we will evaluate the same outcomes.

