#### Attachment systems

After eight weeks, participants will receive their attachment abutments and matrix components will be fitted into mandibular dentures. At this point participants will receive one of the following attachment systems:A: Novaloc (Valoc, Möhlin, Switzerland), a novel model composed by a PEEK capsule and carbon-coated abutment. The yellow (medium) retentive component will be used in this study.B: Locator system (Zest Anchors, Inc., USA) with pink (medium) retentive components. Selected abutments shall have their external margins 1 mm above the mucosa.

For both attachment systems, dentures will be tested intra-orally to confirm correct seating in centric occlusion and additional room to accommodate the attachment matrix parts will be created as necessary. A spacer will be placed between the cervical part of the implant and matrix as recommended by manufacturers. When the denture is seated passively on the mandibular ridge, the prepared space will receive chemically activated acrylic resin and the dentures will again be positioned in centric occlusion. The overdenture will be removed following polymerization, inspected for any defect, corrected if necessary, and finished. Occlusal contacts will be also checked. Instructions for cleaning and maintenance will be provided to participants before denture delivery.

Each participant will receive one type of attachment randomly and wear it for three months. The attachment will then be changed and the new one worn for another period of three months. Then, each participant will be asked to choose the attachment system s/he wishes to keep.

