### Randomization, allocation, and blinding

The sequence in which each participant will receive the two attachments will be decided by a list of random, computer-generated codes. Sequences will be decided based on the initial system used (ratio: 1:1): (1) A-B; (2) B-A. These codes will be secured in opaque sealed envelopes and one will be opened for each participant immediately before attachment insertion. A researcher not involved with the trial will prepare these codes and envelopes, following a simple randomization method stratified by ridge morphology (favorable - Cawood and Howell’s class III vs unfavorable/others). In spite of eventual imbalances in the number of participants per sequence, simple randomization can preclude prediction of allocation by researchers [26].

Although it will not be possible to blind participants and care providers to the treatments, researchers unaware of the participants’ allocations will conduct the outcomes assessment whenever applicable (blind assessor 1: patient-reported outcomes; blind assessor 2: cost data; refer to “Study Outcomes” below for details). We will also avoid mentioning to participants any expectation regarding performance of one system over the other. Appointments will be organized in such a way as to minimize communication between participants and to prevent potential contamination. We will request that participants keep their attachments confidential and not discuss them with the research member involved in the outcome assessment.

To confirm blinding effectiveness, participants will answer which attachment they think they have (experimental or traditional) at the end of the six-month follow-up and their conviction about the strength of their response from 0 to 10 (“not at all certain” and “extremely certain,” respectively) [27].

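### The 12-month data are to be analysed with the cross-over strategies, but each participant then wears one self-chosen attachment, so an attachment effect at that visit is not a randomized comparison

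*Protocol article*

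**What the plan says.** All references are to the protocol article.

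- **What is randomized.** Randomization, allocation, and blinding: "Sequences will be decided based on the initial system used (ratio: 1:1): (1) A-B; (2) B-A". Only the order of the two systems is allocated at random.
- **How the 12-month attachment is assigned.** Attachment systems: "Then, each participant will be asked to choose the attachment system s/he wishes to keep". Long-term follow-up adds a default: "Some participants might prefer to have no specific preference; in that case, we will keep the last type used". New polymeric components are fitted at that point.
- **What is measured.** Background: "Participants will keep their chosen attachments for another 12-month period and we will evaluate the same outcomes". The Abstract and Study outcomes put the emphasis of this visit on wear, maintenance and adverse events, but Background and Long-term follow-up extend it to all outcomes.
- **How it is analysed.** Long-term follow-up: "The same statistical strategies will be employed for the analysis of these long-term data".
- **What those strategies are.** Statistical analysis: "Mixed linear models will be used to test the effect of interventions and follow-up time (three vs six months), as well their interaction"; for the primary outcome, a second model "testing for the intervention by period interaction"; and "Results will be evaluated according to the intention-to-treat principle". The same section also plans descriptive analysis, a composite of clinical adversities, single-covariate models and imputation.

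Nowhere does the article call the 12-month comparison non-randomized, limit it to description, or adapt the model to it.

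**The concern.** The cross-over model gets its validity from two features: the order of treatments is random, and every participant supplies a value on both attachments. Neither holds at the 12-month visit. Each participant supplies one value, on an attachment picked after trying both. If the cross-over strategy is applied as written, the intervention term becomes a comparison of two groups sorted by preference.

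That sorting is tied to the outcome. People who kept Locator are largely those for whom Locator worked at least as well as Novaloc, and the reverse holds for Novaloc. Each group is rating the system that suits it, so the contrast can understate a real average difference. The groups may also be very unequal in size.

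The risk is that long-term satisfaction, quality-of-life and maintenance results by attachment are read with the authority of a randomized comparison. The Discussion promises evidence-based recommendations from this trial, so the distinction matters to readers.

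**Working it through.** **Step 1: does each strategy carry over?** The article gives no numerical figure for the 12-month analysis to reproduce, so the first check is structural.

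| Strategy in Statistical analysis | Cross-over phase | 12-month visit |
|---|---|---|
| Intervention effect | Both attachments in each participant, random order | One attachment per participant, self-chosen or by default |
| Intervention-by-period carryover test | Two periods | One further period, no second sequence |
| Intention to treat | Follows the randomized sequence | No randomized 12-month attachment to follow |
| Descriptive analysis, composite of adversities | Applies | Applies |

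The no-preference default does not restore randomization. For those participants the attachment does follow from the randomized order, but membership of that subgroup is decided after treatment, and the rule pools them with true choosers.

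**Step 2: how far can the chooser contrast be from the average effect?**

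Inputs from Sample size estimation: difference 10 mm; SD of the difference 7.5 mm; planned total 26. Assumptions, not in the article: normal differences, the higher-rated attachment is kept, effects are stable to 12 months, and preference is unrelated to a participant's overall level of rating.

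Let d be the Novaloc minus Locator difference, with mean 10 and SD 7.5.

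- 10/7.5 = 1.333; normal density there 0.1640; P(d < 0) = Φ(−1.333) = 0.0912.
- Expected split: 26 × 0.0912 = 2.4, so about 24:2.
- Mean of d among Novaloc-keepers: 10 + 7.5 × 0.1640/0.9088 = 11.35 mm.
- Mean of d among Locator-keepers: 10 − 7.5 × 0.1640/0.0912 = −3.49 mm.
- With scores m + d/2 on Novaloc and m − d/2 on Locator, the expected group contrast is (11.35 − 3.49)/2 = **3.9 mm**, against a true mean effect of 10 mm.

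That treats all 7.5 mm as stable individual preference. If only a fraction r of the variance of d is stable and the rest is measurement error, the two conditional means shrink towards 10 by the factor r, and the contrast is 10 − r × (10 − 3.93) = 10 − 6.07r:

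| r | Expected contrast |
|---|---|
| 1 (all stable preference) | 3.9 mm |
| 0.5 | 7.0 mm |
| 0 (all measurement error) | 10.0 mm |

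The article does not give r, so the range is the result, not either end.

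**Step 3: precision.** Cross-over SE with 26 participants: 7.5/√26 = 1.5 mm. A between-group SE is SD × √(1/24 + 1/2) = 0.736 × SD. The between-participant SD is not in the article. At an assumed 10 mm the SE is 7.4 mm; at 20 mm it is 14.7 mm.

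**The case against.** Four points can be made on the other side.

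**The sentence is short and the article is condensed.** It announces no separate 12-month superiority test and attaches no randomized label, and a fuller analysis plan may exist. A reader might infer that the trial will certainly publish randomized-style p-values for this phase; the article does not say so. What remains is that it states a rule, and the rule as stated carries over an intervention test, a carryover test and intention to treat without qualification. That is different from leaving detail to another document.

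**A valid 12-month attachment comparison is not impossible.** The 12-month visit could be added as a further time level, keeping each participant's two earlier scores. If the choice depends only on those scores, selection is ignorable in a likelihood analysis. In simulation under the assumptions above, a joint model with a person-by-attachment effect recovers 10.0 to 10.1 mm. This stands, with two limits: a model with only a random intercept stays biased (3.9 mm when all variation is stable preference), and choice may also rest on things that were not scored. The article does not specify the model that would be needed.

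**The primary result is untouched.** A reader might infer that the trial's main conclusion is compromised. It is not: the primary outcome is satisfaction after three months with each attachment, and that comparison keeps its randomized order and its within-participant contrast.

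**The choice is disclosed, and description is legitimate.** The article says openly that participants keep their chosen system, and describing wear and maintenance by attachment kept is sound. This lowers the severity but does not make the sentence correct.

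**Conclusion.** The concern holds for the long-term phase. Applied as written, the cross-over strategies would yield a 12-month intervention effect that contrasts self-selected groups, together with a carryover test and an intention-to-treat rule that have no counterpart there.

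The size cannot be fixed from the article. With the planning values and the higher-rated attachment kept, the expected contrast lies between about 3.9 mm and 10 mm for a true 10 mm effect, with a split near 24:2. The 3.9 mm figure is the extreme case and should not be read as a forecast. The standard error at that split, 7.4 to 14.7 mm, rests on assumed between-participant SDs of 10 and 20 mm. The structural conclusion needs none of these figures.

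Severity: should be fixed, secondary phase only.

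**What to change.** Replace the sentence in Long-term follow-up with wording such as:

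> Twelve-month data are analysed as an observational cohort by attachment kept. Maintenance and adverse events are reported as rates per attachment-year with confidence intervals, and satisfaction and OHIP-EDENT as within-participant change from the three-month score on the same attachment, interpreted as the combined effect of time and new polymeric components. Any between-attachment comparison at 12 months is exploratory, labelled non-randomized, and uses each participant's earlier scores on both attachments. Confirmatory attachment inference is confined to the randomized cross-over periods. Participants without a preference are tabulated separately.

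The within-participant change is labelled this way because it measures time and fresh components, not Novaloc against Locator.

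Cost: a wording change, with no new visits or outcome measures. Choice of attachment is already a listed outcome; the record only has to separate those with no preference from those who chose. The 12-month phase gives up a confirmatory between-attachment p-value.
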